#### **(2) Statistical analysis methods**

Participants who can no longer be contacted during the follow-up will be treated as censored when they were last contacted. Discontinuation of the study participation will not be considered a termination, thus observation will continue.

For the primary endpoint analysis, a survival function will be estimated for each group using the Kaplan-Meier method, which will be used to estimate survival rates and 95% confidence intervals at 6 and 12 months. Group comparisons will be made using stratified log-rank tests (two-sided) with stratified age groups (65-74, 75-84, 85+) as the strata. The significance level is set at 0.05. The baseline hazard will be stratified based on age group strata, and the hazard ratio and its 95% confidence interval will be calculated for the intervention group compared to the usual care using a Cox regression model with the time until rehospitalization, unscheduled hospital visit, or all-cause death as the outcome variable and the allocation group as the explanatory variable.

The same analysis as above will be performed for each of the time to rehospitalization, unscheduled visits, and all-cause mortality, which comprise the primary composite endpoint. The planned statistical tests are unadjusted for the multiplicity.

Subgroup analysis of the primary endpoint will be performed for each index disease (heart failure, pneumonia, diabetes, stroke, urinary tract infection) and drug class (antiplatelet/anticoagulant,

antihypertensive, antidiabetics, sedatives). The 12-month survival rate will be estimated for each subgroup by group and evaluated to see if the difference between groups is in the same direction as the overall analysis.

Details of the analysis methods for secondary endpoints and safety endpoints will be defined in a separate statistical analysis plan.

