## **15. Sample size calculation and its rationale**

Based on previous studies, we estimate the event rate at 12 months for the primary endpoint to be 30% for the intervention group and 40% for the control group. Assuming equally spaced enrollment and allocation, a total of 423 subjects would be needed for the analysis to have a power of 0.80 with a two-sided test at a significance level of 0.05. We estimate 15-20% exclusion from the analysis and plan to enroll a total of 500 subjects (250 in each group) over the 2-year period.

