##### 8.5.1.2 Event rate

The survival rate and its 95% confidence interval at 12 month will be calculated using the survival function estimated in 8.5.1.1.

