## 8.6 Subgroup analysis according to index drug class

The analysis will be conducted in the same method as in 8.5, with subgroups based on the use of the following drug classes at baseline: time to any occurrence of rehospitalization, unscheduled visit, or all-cause mortality; time to rehospitalization; time to unscheduled visit; time to all-cause death.

[Index drug class]

Antiplatelets/anticoagulants

Antihypertensives

Antidiabetics

Sedative

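### Subgroup consistency is judged only by the sign of the 12-month difference; neither document plans a subgroup treatment effect with a confidence interval or an interaction estimate

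*Combined protocol and SAP*

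**What the plan says.** Protocol section 14(2) plans subgroup analysis of the primary endpoint by five index diseases and four drug classes. The 12-month survival rate is estimated by arm in each subgroup and "evaluated to see if the difference between groups is in the same direction as the overall analysis". That is the only consistency criterion in either document.

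SAP 8.5 asks for Kaplan-Meier curves by arm within each index disease, and 8.5.1.2 then says: "The survival rate and its 95% confidence interval at 12 month will be calculated using the survival function estimated in 8.5.1.1". SAP 8.6 treats the drug classes alike: "The analysis will be conducted in the same method as in 8.5". The SAP does not repeat the direction criterion. It extends the output from the primary endpoint to its three components, giving 9 × 4 = 36 sets of per-arm estimates.

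Neither document plans a subgroup hazard ratio, an interval for the between-arm difference, or an interaction estimate or test. Neither gives subgroup sizes, says whether a patient can belong to more than one index disease, or says how a reversed direction would be interpreted.

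**The concern.** Whether an effect is consistent across subgroups depends on how far the subgroup effects differ and how precisely that is known. The sign of a difference carries neither piece of information, and it can mislead in two ways.

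- A uniform benefit can show the wrong sign in a small subgroup by chance, which invites the reading that the intervention does not work for that disease or drug class.
- A subgroup whose benefit is much smaller or larger than the rest, but has the same sign, counts as consistent. That is false reassurance.

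The per-arm intervals in the SAP show that each rate is imprecise, but they are not intervals for the treatment effect or for its variation between subgroups.

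**Working it through.** **Inputs.** Section 15 of the protocol assumes 12-month event rates of "30% for the intervention group and 40% for the control group", "power of 0.80 with a two-sided test at a significance level of 0.05", and states that "a total of 423 subjects would be needed for the analysis". It also says "We estimate 15-20% exclusion from the analysis" and gives the "plan to enroll a total of 500 subjects (250 in each group) over the 2-year period". The analysed sample is therefore 500 × 0.80 = 400 to 500 × 0.85 = 425, or at most 500. Subgroup sizes are not given and are varied below as assumptions.

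**The plan's own figure.** Under exponential survival the hazard ratio is ln 0.70 / ln 0.60 = 0.698. Schoenfeld's formula gives 4(1.960 + 0.842)² / (ln 0.698)² = 244 events. With two years of uniform accrual and everyone followed until one year after the last enrolment, the mean event probability is 0.562. Then 244 / 0.562 ≈ 435, within 3% of 423. Section 13 gives each participant one year of follow-up, so that schedule is a separate question. Here the figure only fixes the effect size and the scale of the sample.

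**One subgroup.** Take a true 10-point benefit, n patients split equally and no censoring. The standard error of the difference is √(0.30×0.70/(n/2) + 0.40×0.60/(n/2)) = √(0.90/n), and P(wrong sign) = Φ(−0.10/√(0.90/n)).

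| n | SE | P(wrong sign) |
|---|---|---|
| 40 | 0.150 | 25% |
| 60 | 0.122 | 21% |
| 85 | 0.103 | 17% |
| 200 | 0.067 | 7% |

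**At least one of nine.** The subgroups share one sample, so multiplying these probabilities is not exact. The criterion was simulated as written, comparing each subgroup's sign with the observed overall sign. The true benefit was 10 points everywhere, 400-500 patients were analysed, and 4,000-5,000 trials were run per scenario (Monte Carlo SE at most √(0.25/4000) = 0.8 points).

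| Assumed share of sample, each disease | Assumed share, drug classes | At least one reversal | Same, given significant overall benefit |
|---|---|---|---|
| 5% | 20-50% | 85-88% | 79-83% |
| about 10% | 25-75% | 75-80% | 66-69% |
| 20%, mutually exclusive | 50-75% | 55-62% | 38-42% |
| 20%, overlapping | 50% | 51-57% | 35-39% |
| 25%, overlapping | 50% | 44-51% | 26-28% |
| 30%, overlapping | 50% | 37-45% | 19-21% |
| 50%, overlapping | 75% | 16-22% | about 3% |

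If the true benefit were 5 points, the figure would be 90% (N = 500, diseases 10% each).

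**What the sign cannot see.** A subgroup with no true effect points towards benefit with probability Φ(0) = 50%, so where the overall result shows benefit it would be called consistent about half the time.

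**What an interaction estimate can deliver.** For a subgroup with share q, the SE of the difference between the effects in patients with and without the condition is √(0.90/(N·q(1−q))).

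- N = 400, q = 0.10: √(0.90/36) = 0.158, 95% half-width 31 points, power for a 10-point interaction about 10%.
- N = 500, q = 0.50: √(0.90/125) = 0.085, half-width 17 points, power about 22%.

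Nine independent tests at 0.05 give 1 − 0.95⁹ = 37% chance of at least one false positive.

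**The case against.** The strongest reply is that little hangs on this check. The protocol says only that direction will be evaluated. No claim or treatment consequence follows from a reversal, the SAP output is descriptive, and the primary test and hazard ratio do not depend on it. That stands, and it limits the consequence to over-reading or false reassurance in the report.

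A reader might infer that the criterion will usually produce a spurious reversal. The documents do not support that as a general statement. It applies to at least one of nine, not to a given subgroup, and it depends on sizes they do not state. Multiplying probabilities as if subgroups were independent gives 67-85% for disease subgroups of 40-85 and drug-class subgroups of 150-250 patients. That ignores the shared sample and leaves out larger, overlapping diseases. SAP 8.7 lists the presence of each index disease, which allows overlap. Given a significant overall benefit, where a reversal would mislead most, the chance passes one half only for small disease subgroups.

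A reader might also count the SAP output as 36 unadjusted comparisons. It specifies no between-arm contrast or test, so these are 36 sets of per-arm estimates, and labelling the 27 component sets descriptive would change nothing.

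Finally, an interaction test would itself have low power. That is correct, and it is why the estimate and its interval should lead and the p-value should be secondary.

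**Conclusion.** The point holds as a cheap improvement to analysis and reporting. The protocol's sole consistency criterion ignores precision, and the SAP supplies nothing that estimates how the treatment effect varies between subgroups.

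Under a uniform 10-point benefit, a single subgroup reverses in about 25% of trials at 40 patients and 7% at 200. At least one of nine reverses in roughly 50-88% of trials when each disease is 20% of the sample or smaller, and in about 16-45% when diseases overlap at 30-50% each. These figures rest on the planned event rates, 400-500 analysed, no censoring, and assumed subgroup sizes and overlap.

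The documents do not support calling this a decision rule that would produce false claims of harm. It could invite over-reading or false reassurance, and the primary analysis is unaffected.

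**What to change.** For the primary endpoint, replace the same-direction criterion as follows.

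- Fit the age-stratified Cox model already specified in protocol 14(2) and SAP 8.1.5, adding the subgroup indicator and its interaction with arm, one model per disease or drug class.
- Report the hazard ratio with 95% interval in patients with and without each condition, and the ratio of hazard ratios with its 95% interval.
- Give the interaction p-value as secondary and exploratory. State that power is low (about 10-22% for a 10-point interaction) and that there is no multiplicity adjustment.
- State the subgroup sizes and whether the index diseases may overlap.
- The SAP revision history shows that analysis had already been conducted when version 1.2 was written. Models added after that analysis must be disclosed as post hoc.

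The cost is a change of SAP text and one extra model per subgroup, with no new data. The downside is wide intervals, which show how little the trial can say about individual subgroups.

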## **15. Sample size calculation and its rationale**

Based on previous studies, we estimate the event rate at 12 months for the primary endpoint to be 30% for the intervention group and 40% for the control group. Assuming equally spaced enrollment and allocation, a total of 423 subjects would be needed for the analysis to have a power of 0.80 with a two-sided test at a significance level of 0.05. We estimate 15-20% exclusion from the analysis and plan to enroll a total of 500 subjects (250 in each group) over the 2-year period.

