### **13. Duration of the study**

The enrollment period for the study is planned to be 3 years and 3 months from the Institutional Ethical Committee approval, but may be extended or terminated earlier depending on the status of enrollment. The follow-up period for each subject will be one year.

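### With the protocol's fixed 12-month follow-up, 423 analysed patients give about 59% power for 30% vs 40%, not the stated 80%, and all 500 give about 66%

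*Combined protocol and SAP*

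**What the plan says.** Protocol section 15, repeated in SAP 2.2, sets out the planning assumptions:

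- Event rates: "we estimate the event rate at 12 months for the primary endpoint to be 30% for the intervention group and 40% for the control group".
- Error rates: power 0.80 "with a two-sided test at a significance level of 0.05".
- Accrual: "Assuming equally spaced enrollment and allocation".
- Result: "a total of 423 subjects would be needed for the analysis to have a power of 0.80".
- Margin: "We estimate 15-20% exclusion from the analysis and plan to enroll a total of 500 subjects (250 in each group) over the 2-year period".

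Neither section states the length of follow-up or the formula behind 423.

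The design itself is explicit about follow-up. Protocol section 13 says "The follow-up period for each subject will be one year". Section 6(3) ends participation when the 12-month follow-up is complete. Section 8(3) counts deaths, unscheduled visits and rehospitalizations up to 12 months after allocation. Allocation is 1:1 (section 6(5)), and the primary test is a two-sided log-rank test stratified by age group (section 14(2), SAP 8.1.3).

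**The concern.** For a log-rank test, power depends on the number of events. If each patient is observed for 12 months and the 12-month event rates are 30% and 40%, about 35% of patients overall have an event. With 423 patients that is far fewer events than a hazard ratio near 0.70 requires. The mention of evenly spaced enrolment is also odd, because the accrual pattern has no bearing on power when everyone has the same fixed follow-up.

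This is the only power statement for the primary comparison. If it is wrong, a null result would be read as carrying a 20% risk of having missed the planned effect, when that risk is about 34 to 43%.

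**Working it through.** **Inputs.** Rates 0.30 and 0.40 at 12 months, two-sided 0.05, power 0.80 and 423 analysed come from protocol section 15. The 1:1 allocation is in section 6(5). Twelve months of follow-up per patient is in sections 6(3), 8(3) and 13. Proportional hazards is assumed, as in the planned Cox model.

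**Step 1. Hazard ratio and events needed.**

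- HR = ln(0.70)/ln(0.60) = 0.698; |ln HR| = 0.3592.
- Schoenfeld: events = 4 × (1.960 + 0.8416)² / 0.3592² = 243.3.
- Freedman: 248.6.

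**Step 2. Trying to reproduce 423.** N is events divided by the mean event probability over the two arms. The scenarios with staggered entry also assume exponential survival.

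| Follow-up assumed | P(event), intervention / control | Mean | N (Schoenfeld) |
|---|---|---|---|
| 12 months each (the protocol) | 0.300 / 0.400 | 0.350 | 695 |
| 2 years each | 0.510 / 0.640 | 0.575 | 423 |
| 1-year uniform accrual, then 1.5 years more | 0.507 / 0.636 | 0.572 | 426 |
| 2-year uniform accrual, then 1 year more | 0.4995 / 0.6241 | 0.562 | 433 |
| 3.25-year uniform accrual, then 1 year more | 0.586 / 0.707 | 0.646 | 376 |

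The 2-year row uses 1 − 0.70² = 0.51 and 1 − 0.60² = 0.64, so 243.3/0.575 = 423. Several longer follow-ups therefore land on or near 423.

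At 12 months no standard two-sided method does. Freedman gives about 710, two proportions 712 pooled and 708 unpooled, arcsine 712, and the continuity-corrected version 752. One-sided variants give 549 to 600.

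**Step 3. Power under the actual follow-up.** Power = Φ(√(d/4) × 0.3592 − 1.960), with d = 0.35 × N.

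| Analysed | Events d | √(d/4) × 0.3592 | Power |
|---|---|---|---|
| 400 (500 less 20%) | 140 | 2.125 | 0.566 |
| 423 | 148 | 2.185 | 0.589 |
| 500 | 175 | 2.376 | 0.661 |

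Other methods agree. At 423, Freedman gives 0.580, two proportions 0.578, and a log-rank simulation of 10,000 runs 0.576. At 500 they give 0.652, 0.650 and 0.658.

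**Step 4. Effect detectable with 80% power at 12 months.** Hold the control rate at 40% and solve for the intervention rate p at which √(d/4) × |ln HR| = 2.802, where d = N × (p + 0.40)/2. With 423 analysed, p = 27.3% (HR 0.63). With 500, p = 28.3% (HR 0.65).

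**Step 5. Exclusion margin.** 423/0.85 = 498, which 500 covers. 423/0.80 = 529, which it does not; 500 × 0.80 = 400.

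**The case against.** **The cause is not documented.** A reader might infer that the calculation took two years of uniform accrual with everyone followed to a common study end, and that this explains the evenly spaced enrolment. The documents do not support that as a finding. The scenario gives 433 rather than 423, a common two-year follow-up fits better, and neither section states the follow-up used. What stands is narrower: 423 needs follow-up well beyond the one year that the protocol allows.

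**59% is not the only fair figure.** The analysis rules remove only participants later found ineligible (section 14(1), SAP 3). Those lost to contact are censored, not dropped, and observation continues after discontinuation (section 14(2)). Section 16 adds destruction of data after consent withdrawal. The analysed number could therefore exceed 423. This is a fair point, and it is why power is given as a range. But 66% with all 500 is the ceiling for the planned effect, and the 15-20% exclusion is the plan's own estimate.

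**The enrolment period looks contradictory.** Section 15 speaks of two years, whereas section 13 says "The enrollment period for the study is planned to be 3 years and 3 months". It is tempting to treat this as part of the power error. It is not: the protocol's revision history records study-period extensions because enrolment was delayed, section 13 allows extension, and accrual length does not affect power when follow-up is fixed at 12 months. At most the wording was not updated.

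**Exclusion margin.** 500 meets the lower end of the stated range and misses the upper. Going from 423 to 400 lowers power only from 0.589 to 0.566, so this is secondary.

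**No bias.** The error does not affect the estimate, its confidence interval or the type I error. That is correct; it affects the power claim and how a null result is read.

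**Conclusion.** The stated power is wrong for this design. For 30% vs 40% at 12 months with one year of follow-up per patient, power is about 57% with 400 analysed, 59% with 423 and 66% with 500, against the stated 80%. Reaching 80% would take about 695 to 712 analysed patients, roughly 1.6 to 1.7 times 423.

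Under proportional hazards these power figures depend only on the two 12-month rates and not on the shape of the hazard. The exponential assumption enters only in the staggered-entry scenarios used to look for the origin of 423. The figures ignore censoring before 12 months, which would lower power further, and use the unstratified formula as an approximation to the age-stratified test. They are conditional on the planned rates; different true rates would give a different power.

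How 423 was obtained remains unknown.

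**What to change.** Add a dated correction to protocol section 15 and SAP 2.2 and leave the existing planning text visible. The SAP revision history shows that version 1.2 was written after the analysis had been conducted, so deleting or silently replacing the planning basis now would obscure what was pre-specified. The correction should state:

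- With 12 months of follow-up per patient, the planned size gives about 57 to 66% power for 30% vs 40% (400 to 500 analysed; 140 to 175 expected events).
- The effect detectable with 80% power is 40% vs about 27 to 28% (HR about 0.63 to 0.65, for 423 to 500 analysed).
- The follow-up assumption and method behind 423, if the sponsor can recover them.
- 500 enrolled covers 15% exclusion from 423 but not 20%.

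A non-significant primary result should not be described as coming from an 80%-powered trial. It should be interpreted through the hazard ratio and 95% confidence interval, which are already planned (protocol section 14(2), SAP 8.1.4 and 8.1.5). The enrolment-period wording in sections 13 and 15 can be aligned at the same time for consistency.

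The cost is a short text change and a less favourable stated power. No new patients and no change to the analysis are needed.

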## (5) Case registration and allocation methods

### 【Allocation methods】

Patients will be assigned to the deprescribing intervention group and usual care group in a 1:1 ratio by a stratified block randomization method. The allocation factors will be age groups (65-74 years, 75-84 years, and 85 years and older).

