#### **(1) Analysis set**

The analysis of the primary and secondary endpoints will include all study participants enrolled in the study. If it is found that the eligibility criteria are not met after the start of the study, they will be excluded from the analysis. The analysis of the safety endpoints will be performed on all participants enrolled in the study.

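### Enrolling 500 meets the 423 target only up to 15.4% exclusion, not across the plan's own 15–20%, and the plan does not say who the excluded patients are

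*Combined protocol and SAP*

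**What the plan says.** Protocol section 15, repeated word for word in SAP 2.2, sets out the sample size in three steps.

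- Assumed rates: "we estimate the event rate at 12 months for the primary endpoint to be 30% for the intervention group and 40% for the control group".
- Target: "a total of 423 subjects would be needed for the analysis", to give "power of 0.80 with a two-sided test at a significance level of 0.05".
- Allowance: "We estimate 15-20% exclusion from the analysis and plan to enroll a total of 500 subjects".

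Neither place says which patients make up the 15–20%.

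The rules on who is analysed are elsewhere.

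- Section 14(1): "The analysis of the primary and secondary endpoints will include all study participants enrolled in the study". The one exception is patients found after the start not to meet the eligibility criteria. SAP section 3 gives the same rule and the same exception.
- Section 14(2): "Participants who can no longer be contacted during the follow-up will be treated as censored when they were last contacted". Patients who discontinue continue to be observed.
- Section 16: if consent is withdrawn, the clinical information already collected is destroyed and not used.

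**The concern.** An enrolment figure that carries an allowance for exclusions should still deliver the required number at the top of the stated allowance, or the plan should say that it does not. Here a reader is told that 423 are needed, that up to 20% may be excluded, and that 500 will be enrolled, and will take it that 500 is enough throughout.

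The allowance also stands apart from the analysis rules. In many plans a figure of this kind stands for loss to follow-up, but section 14(2) keeps lost patients in the analysis as censored. The routes that do remove a patient are ineligibility and data destruction after withdrawal, and section 15 mentions neither. Whether 15–20% is a sensible allowance therefore cannot be judged. At stake are the accuracy of the stated power and a clear account of who leaves the primary analysis.

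**Working it through.** **Inputs.** Section 15 and SAP 2.2: 423 analysed, 80% power, two-sided 0.05, 12-month event rates of 30% and 40%, 500 enrolled, 15–20% excluded. Section 6(5): 1:1 allocation. Section 13: one year of follow-up per patient.

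**1. The plan's 423.** With constant hazards the hazard ratio is ln(0.70)/ln(0.60) = 0.698. Schoenfeld's formula, 4 × (1.960 + 0.842)² / (ln 0.698)², gives 244 events.

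- One year of follow-up for everyone: the mean event probability is (0.30 + 0.40)/2 = 0.35, so N = 244/0.35 = 697. Freedman's formula gives 711 and a comparison of two proportions 712. None is near 423.
- Uniform accrual over two years with follow-up to a common close one year later (an assumption that the documents do not state): the event probabilities are 0.500 and 0.624, and N = 433, which is 2.4% above 423.

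So 423 is approximated only if follow-up runs past 12 months. The steps below take 423 as the plan's own target.

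**2. The plan's 500.** Required enrolment is 423/(1 − d), where d is the excluded fraction.

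- d = 0.15: 423/0.85 = 497.6, that is 498. This reproduces 500 to within two patients.
- d = 0.20: 423/0.80 = 528.75, that is 529. This is 29 more than planned.

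**3. What 500 leaves.**

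| Excluded | Analysed | Against 423 |
|---|---|---|
| 15% | 500 × 0.85 = 425 | +2 |
| 15.4% | 500 × 0.846 = 423 | 0 |
| 20% | 500 × 0.80 = 400 | −23 |

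Break-even is 1 − 423/500 = 15.4%. The target is missed over 20 − 15.4 = 4.6 of the five percentage points in the range.

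**4. Power at 400, relative to the plan's calibration.** If 423 gives 80%, power at n is Φ((1.960 + 0.842) × √(n/423) − 1.960). This gives 80.2% at 425 and 77.8% at 400.

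The drop is about the same size under either design in step 1, although the level is not:

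| Design | Power at 423 | Power at 400 |
|---|---|---|
| Fixed one-year follow-up | 0.589 | 0.566 |
| Two-year accrual, common close one year later | 0.791 | 0.768 |

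**5. Exclusion is not the same as censored loss.** Take the fixed one-year follow-up. Excluding 100 patients outright leaves 400 × 0.35 = 140 events. If instead 20% of 500 are lost at a constant rate over the year and censored (an assumption), the mean event probability is 0.316 and about 158 events remain. The 400-patient figure therefore applies to true exclusions only.

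**The case against.** The strongest reply is that 15–20% is a rounded planning estimate, that 500 is right for its lower end, and that missing by 23 patients at the upper end costs about two points of power. The analysis set is already fixed by section 14(1) and SAP section 3, so no analysis would change. All of that stands as to size. It does not rescue the statement as written: the range is the plan's own, and 500 falls short over nearly all of it.

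A reader might infer more: that section 15 sets up a second analysis population, smaller than the one in section 14, and that patients lost to follow-up are to be dropped along with the events seen before their loss. The documents do not support this. The protocol and SAP give one consistent analysis set. Section 15 is a planning allowance that defines no population, and section 14(2) expressly censors lost patients.

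Nor can it be said that the 15–20% must consist of losses. Later-found ineligibility and data destruction after withdrawal are real routes to exclusion. The documents give no expected share for either, so whether together they could reach 15–20% cannot be checked from the documents.

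**Conclusion.** The point holds as an arithmetic shortfall with an unexplained allowance. The arithmetic uses only the plan's own figures: 500 covers exclusion up to 15.4%, and at 20% it leaves 400 against a target of 423. The consequence is small, about 78% power in place of 80%.

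The 78% should not be read as the trial's actual power. It rests on the plan's statement that 423 gives 80%, which the fixed one-year follow-up in section 13 does not reproduce. That is a larger question than this one and needs its own check. Nor does the 78% apply to loss to follow-up, since censored patients still contribute time and events.

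**What to change.** Keep enrolment at 500. In protocol section 15 and SAP 2.2, restate the allowance along these lines:

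> 500 enrolled meets the 423 target for exclusions up to about 15%. At 20% exclusion 400 are analysed, below 423, with power of about 78% if 423 gives 80%.

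Then add who counts: exclusions are patients found ineligible after the start (section 14(1), SAP section 3) and patients whose data are destroyed after consent withdrawal (section 16). Patients lost to follow-up are censored under section 14(2) and are not excluded. Section 9 lists consent withdrawal among the reasons for discontinuation, and section 14(2) continues observation after discontinuation, so the same sentence should say that section 16 governs withdrawals that lead to data destruction.

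Keep the condition attached to the 78% until the 423 has been checked against the one-year follow-up.

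The cost is a few sentences in two places and a slightly less favourable stated power at the 20% end. No further patients are needed, and the analysis set and method are unchanged.
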